### Qualitative data analyses

With regard to the qualitative aim to examine barriers and facilitators of treatment implementation and employment outcomes via a 90-min semi-structured interview, we will recruit participants from both study arms that reaches a sample size sufficient for data saturation to occur through a thematic analysis [39]. Transcribed interview data will be reviewed by three study team members experienced in qualitative data analysis procedures. These independent analysts will use an inductive process to explore themes to identify the contextual implementation barriers and facilitators, followed by the creation of subthemes as guided by the data. If analysts identify what appear to be new themes during the coding process, a deductive approach will be used to determine if these newly identified themes inform the existing themes (i.e., act as a sub-theme) or extend the main themes. We will use a combined inductive-deductive approach to coding that is based in the situational context of the data [40].

### MOUD analyses

An additional aim is to compare IPS to non-IPS-VR in terms of adherence to MOUD and relapse into heavy opiate use. We expect that MOUD adherence can be treated as a continuous variable in regression models. However, prior to modeling we will examine its distribution, to determine if this is appropriate. Relapse will be treated in two ways, as a binary indicator if any relapse as determined by TAPS (defined as opioid misuse ≥ 4 times/mo.), and the total number of self-reported days of misuse. The first dichotomous outcome will require logistic regression. The second approach will depend on the observed distribution and may be treated as either negative binomial or continuous. We will also explore the differences between groups in rates of relapse. The exploratory analysis will construct longitudinal models similar to those in our first aim considering outcomes of weekly adherence and relapse with that week’s employment status as well as lagged employment status (e.g., employment in previous weeks) as covariates to more directly examine the possible role of employment outcomes in explaining adherence and/or relapse. Further analyses may also include psychosocial covariates.

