### Overview of design, aims, and hypotheses

The purpose of this study is to evaluate the efficacy of IPS provided to veterans with OUD using a mixed methods approach. Our first aim is to conduct a prospective, multi-site, RCT to determine the efficacy of IPS compared to treatment-as-usual non-IPS vocational rehabilitation (non-IPS-VR). Consenting and eligible veterans who are currently unemployed or under-employed and are in treatment for OUD are randomized to either IPS or non-IPS-VR. Each participant receives IPS or non-IPS-VR and have outcomes assessed for 18 months. We hypothesize that participants who receive IPS will have significantly more weeks worked in a competitive job over 18 months compared to non-IPS-VR services. We also hypothesize that compared to non-IPS-VR, IPS recipients will earn significantly more income from competitive jobs and be significantly more likely to achieve steady employment, defined as working in a competitive job for 50% of the 18-month period. Our second aim is to explore and identify contextual barriers and facilitators of implementing rehabilitation services in both study arms and to achieving competitive employment among veterans with OUD. We will evaluate the implementation and employment challenges, optimal functioning, and OUD treatment adherence. We are employing a community-based participatory research (CBPR) approach to achieve this aim. True to CBPR approach, the interview guide for the present study was developed through an iterative interview process with various stakeholders, including employers of individuals with OUD, IPS and vocational rehabilitation specialists, Veterans, and researchers with expertise in this field. These various stakeholders were asked to identify various contextual barriers and facilitators of employment for Veterans with OUD. From these interviews, various overarching themes were developed to guide the development of the interview guide to further explore Veterans perspectives in the current study. The fundings of the barriers and facilitators will be published in a separate manuscript. For this study, we are also utilizing an iterative process of qualitative individual interviews with veterans with OUD that were randomized to IPS or non-IPS-VR. Our final aim is to evaluate the impact of IPS compared to non-IPS-VR on adherence to medications for OUD (MOUD) and rates of OUD relapse. We hypothesize that compared to non-IPS-VR, veterans who receive IPS will be significantly more likely to adhere to MOUD (i.e., those on MOUD only) and to have lower rates of OUD relapse.

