### Clinical assessments

At baseline, the Clinical Research Coordinator (CRC) collects baseline demographics and characteristics, including age, gender, race, ethnicity, marital status, education level, military history (i.e., branch, period of service, combat exposure), status of housing and transportation, status of VA and non-VA disability, psychiatric treatment history, past and current treatment for OUD, and work history, including length of unemployment, type of previous job(s), and longest duration of competitive work. The Mini-International Neuropsychiatric Interview for DSM-5 is conducted by an investigator or CRC to confirm OUD diagnosis and document comorbidities [23]. Repeated measures include: the Patient Health Questionnaire-9 (PHQ-9) [24]; the Generalized Anxiety Disorder Scale (GAD-7) [25]; Brief Resilience Scale (BRS) [26]; Perceived stress Scale-10 (PSS-10) [27]; Quality of Life Scale (QOLS) [28]; Community Assessment Inventory (CAI) [29]; Alcohol Abstinence Self-Efficacy (modified for OUD) [30]; the Tobacco, Alcohol, Prescription Medications, and Other Substance (TAPS) Part-2 Tool [31]; and the Columbia Suicide Severity Rating Scale (C-SSRS) [32].

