### MOUD outcome assessment

We are allowing Veterans on all types of MOUD (e.g., methadone, suboxone, naltrexone etc.) to be part of the study. We will ensure that type of MOUD will be controlled for in all statistical models at the end of the study. Adherence and relapse (i.e., opioid misuse ≥ 4 times/month) will be measured using the TAPS-2 Tool and pharmacy records. Adherence is defined as the number of days MOUD was received as indicated during the last 4 weeks of the intervention period.

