### Primary outcome analysis

The target sample size is 120 randomized participants (60 per study arm). The sample size was based on our most recent IPS study at the Tuscaloosa VA Medical Center that evaluated IPS in the primary care setting as nearly half of the participants had a SUD diagnosis. We expect that more than 84% will complete the intervention as randomized and greater than 95% will provide analyzable employment data. The between-group effect size was 0.55 in favor of IPS in the prior study, for which our projected sample size (54 per group with > 2 months data) would provide > 81% power. Very conservatively assuming that only 90% provide analyzable data this yields approximately 54 participants per group. This provides 80% power to detect a difference in means between groups of 0.54 standard deviations for a continuous outcome. The primary employment outcome is the number of weeks with competitive employment over the 18-month follow-up period. A week scored as “worked” is one in which a competitive job was held for any number of hours or days during that week. A week scored as “not worked” is one in which there was no competitive job held, or there were no employment data (i.e., early exit or missing data). The analysis of the primary outcome will use longitudinal mixed-effects regression models considering the cumulative number of weeks worked at each assessment as the dependent variable and study arm (IPS vs. non-IPS-VR) as the main independent variable adjusted for gender. Study site will be treated as a random effect, as will participant to account for the nesting of participants within sites and the multiple observations per person. We will initially specify the covariance structure of the repeated outcomes as unstructured and will proceed respectively to autoregressive and exchangeable structures if convergence issues are encountered. Prior to final modeling we will examine longitudinal plots of the employment data by group to evaluate whether the most appropriate model and any possible interaction effect appears to be additive (linear regression) or multiplicative (suggesting negative binomial regression), whether time should be included as categorical or linear, and whether it appears that a group*time interaction term is required to faithfully model the data.

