VA Service-Connected Disability Status						
None	10	40.0	6	37.5	16	39.0
Filing for the first time	2	8.0	1	6.3	3	7.3
Filing for appeal	–	–	1	6.3	1	2.4
Receiving any SC disability	10	40.0	8	50.0	18	43.9
Filing for increase	3	12.0	–	–	3	7.3
Receiving 100% SC	6	24.0	3	18.8	9	22.0
Employment Status						
Unemployed	21	84.0	14	87.5	35	85.4
Underemployed	4	16.0	2	12.5	6	14.6
Number of Competitive Jobs Held in the Last 3 Years						
Zero	12	48.0	8	50.0	20	48.8
One	4	16.0	5	31.3	9	22.0
Two	6	24.0	–	–	6	14.6
Three or more	3	12.0	3	18.8	6	14.6
Financial Dependents						
Zero	3	12.0	1	6.3	4	9.8
One	10	40.0	9	56.3	19	46.3
Two	5	20.0	5	31.3	10	24.4
Housing						
Single-family Home	6	24.0	4	25.0	10	24.4
Mobile Home	1	4.0	1	6.3	2	4.9
Apartment or Condominium	5	20.0	2	12.5	7	17.1
Renting Room	3	12.0	1	6.2	4	9.8
Transitional housing	3	12.0	3	18.7	6	14.6
Homeless shelter	3	12.0	4	25.0	7	17.1
Motel	1	4.0	–	–	1	2.4
Residential Treatment	3	12.0	1	6.3	4	9.8
Locality						
Urban	19	76.0	13	81.3	32	78.0
Rural	4	16.0	3	18.8	7	17.1
No response	2	8.0	–	–	2	4.9

*SSI* Social Security Income, *SSDI* Social Security Disability Income, *SC* Service-Connected

**Table 3 Tab3:** Baseline Opioid Use and Treatment History

Variable	IPS (*N* = 25)		Non-IPS-VR (*N* = 16)		Total (*N* = 41)	
	*M*	*SD*	*M*	*SD*	*M*	*SD*
Duration of OUD (years)	10.2	7.9	10.4	12.7	10.3	9.8
	Frequency	Percent	Frequency	Percent	Frequency	Percent
Types of Opioids Used						
Prescription pain pills	19	76.0	11	68.8	30	73.2
Street-derived pills	10	40.0	8	50.0	18	43.9
Street-derived IV, not heroin	2	8.0	1	6.3	3	7.3
Heroin	8	32.0	5	31.3	13	31.7
Current OUD Treatment (past 12 months)						
Any Treatment	21	84.0	10	62.5	31	75.6
Medications for OUD	12	48.0	4	25	16	39.0
Other psychotropic medication	3	12.0	1	6.3	4	9.8
Supportive group therapy	9	36.0	3	18.8	12	29.3
Supportive individual therapy	8	32.0	7	43.8	15	36.6
Complimentary	3	12.0	1	6.3	4	9.8
Inpatient	1	4.0	2	12.5	3	7.3
Residential	5	20.0	5	31.3	10	24.3
Outpatient	2	8.0	2	12.5	4	9.8
OUD Treatment prior to 12 months						
Any Treatment	18	72.0	9	56.3	27	65.8
Medications for OUD	9	36.0	6	37.5	15	36.6
Other psychotropic medication	2	8.0	1	6.3	3	7.3
Supportive group therapy	8	32.0	6	37.5	14	34.1
Supportive individual therapy	8	32.0	8	50.0	16	39.0
Complimentary	1	4.0	3	18.8	4	9.8
Inpatient	6	24.0	4	25.0	10	24.4
Residential	5	20.0	4	25.0	9	22.0
Outpatient	2	8.0	–	–	2	4.8
MINI International Neuropsychiatric Interview						
Major Depressive (current)	3	12.0	1	6.3	4	9.8

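### The MOUD adherence comparison, as described, names no term for adherence before randomisation and so gives up precision in a subset of about 47 participants

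*Protocol article*

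**What the plan says.** All references are to the protocol article.

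- **Hypothesis** (Overview of design, aims, and hypotheses): IPS recipients are expected to be "significantly more likely to adhere to MOUD (i.e., those on MOUD only"), so the comparison is confined to participants on MOUD.
- **Endpoint** (MOUD outcome assessment): "Adherence is defined as the number of days MOUD was received as indicated during the last 4 weeks of the intervention period". This is one count per participant, with possible values from 0 to 28. The sources named for adherence and relapse are the TAPS-2 Tool and pharmacy records.
- **Model** (MOUD analyses): "We expect that MOUD adherence can be treated as a continuous variable in regression models", followed by "However, prior to modeling we will examine its distribution, to determine if this is appropriate".
- **Covariates** (MOUD outcome assessment): "We will ensure that type of MOUD will be controlled for in all statistical models at the end of the study". No other covariate is tied to the adherence comparison.
- **Baseline data** (Clinical assessments): the items collected at entry include "past and current treatment for OUD".
- **Contrast** (Secondary outcomes analysis): for the psychological measures, the baseline score is part of the longitudinal model.
- **Related model** (MOUD analyses): an exploratory longitudinal analysis of weekly adherence uses current and lagged employment as covariates.

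**The concern.** Adherence before randomisation is likely to predict adherence at the end. MOUD type does not stand in for it: type records which medication was taken, not how regularly. Without a prior-adherence term, the part of the end-count variation that entry adherence could explain stays in the residual, and the interval for the arm difference is wider than it needs to be.

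This matters more here than for the primary outcome because the subset is small. Randomisation is stratified by site only, so neither MOUD status nor prior adherence is balanced by design. The article brings baseline values into the psychological-score models but mentions none for adherence. The exploratory weekly model does not fill the gap: it conditions on employment after randomisation, in order to study the role of employment, and names no baseline adherence term.

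What is at stake is the width of the interval around a named hypothesis test, and a choice of covariate that is better settled before outcomes are analysed.

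**Working it through.** **Inputs from the documents**
- Primary outcome analysis: "The target sample size is 120 randomized participants (60 per study arm"); 54 per arm analysable; 80% power at 0.54 SD and more than 81% at 0.55 SD.
- Table 3, MOUD in the past 12 months: 12 of 25 in IPS, 4 of 16 in non-IPS-VR, 16 of 41 overall.
- Alpha 0.05, taken as two-sided (the article does not say).

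**Assumed:** the correlation r between prior and end adherence, which the documents do not give. I use 0.3, 0.5 and 0.7.

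**1. The plan's own figures.** With 54 per arm, SE = sqrt(1/54 + 1/54) = 0.192 SD. By the normal approximation, power is 80.1% at 0.54 SD and 81.5% at 0.55 SD. The noncentral t gives 79.4% and 80.8%, with a detectable difference of 0.544 SD. The stated figures reproduce. They concern the primary outcome; no power is stated for adherence.

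**2. Subset size.** 16/41 = 0.390, and 0.390 × 120 = 46.8, about 47. The Wilson 95% interval for 16/41 is 0.257 to 0.543; multiplied by 120, this is about 31 to 65. If 90% are analysable, 47 becomes about 42.

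**3. Split between arms.** An even split is 23.5 v 23.5. Carrying the present arm rates to 60 per arm gives 0.48 × 60 = 28.8 and 0.25 × 60 = 15, about 29 v 15.

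**4. Detectable difference without adjustment.** Solve for d such that a two-sample t test with n1 + n2 − 2 degrees of freedom and noncentrality d / sqrt(1/n1 + 1/n2) has 80% power.

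**5. With adjustment.** In a linear model, one baseline covariate multiplies the residual SD by sqrt(1 − r²), which is 0.954, 0.866 or 0.714. The detectable difference scales by the same factor.

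| Subset | SE (SD) | Unadjusted | r = 0.3 | r = 0.5 | r = 0.7 |
|---|---|---|---|---|---|
| 23.5 v 23.5 | 0.292 | 0.84 | 0.80 | 0.72 | 0.60 |
| 29 v 15 | 0.318 | 0.91 | 0.87 | 0.79 | 0.65 |
| 21 v 21 (90% analysable) | 0.309 | 0.89 | 0.85 | 0.77 | 0.63 |

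Variance falls by r², that is 9%, 25% or 49%. For 47 participants this is worth 47/(1 − r²), about 52, 63 or 92.

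**6. Power at 0.55 SD**, used only as a yardstick because the article states no adherence effect. At 23.5 v 23.5 it is 45% unadjusted, and 49%, 57% or 73% at the three correlations.

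**7. Chance imbalance at entry.** With 23.5 per arm, the baseline difference in adherence has SE 0.292 SD. A one-SE imbalance moves the unadjusted estimate by r × 0.292, which is 0.09, 0.15 or 0.20 SD. The unadjusted standard error already includes this variation, so it restates the precision loss and is not an additional defect.

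**The case against.** The strongest objection is that the lack of adjustment is read from silence. The MOUD analyses section gives no full covariate list, leaves the model form open, and belongs to a condensed article; a fuller protocol or analysis plan may well include baseline adherence. This stands. The article does not rule the adjustment out, so the point can only be a recommendation to state it.

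Several stronger readings are tempting, and the documents do not support them:

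- **That the comparison is biased.** Under randomisation any entry difference is due to chance, provided being on MOUD is determined at baseline. The article does not say when it is determined, which is why the fix includes it.
- **That the 12 v 4 count shows unequal adherence at entry.** It shows who was taking MOUD, not how regularly, and the two rates (12/25 v 4/16) are compatible with chance (Fisher p = 0.20). Part of the imbalance also comes from the 25 v 16 allocation so far. Projecting 12:4 directly to the full trial would therefore overstate it, and 29 v 15 is the fairer projection. Baseline adjustment would not mend unequal subset sizes in any case.
- **That chance imbalance swamps any plausible effect.** No adherence effect is stated against which to judge this.

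The objection is also right that the size of the gain is uncertain. The two counts would lie about 18 months apart, so the correlation could be low, and at 0.3 the gain is only 0.04 SD. The sqrt(1 − r²) factor assumes a linear model for a bounded count and credits the whole gain to the new covariate, although MOUD type may already explain some of it.

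Feasibility is not shown either. Pharmacy records are a named source, but the article does not say how far back they reach or which dispensers they cover. A participant starting MOUD near entry may have no meaningful prior count.

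What survives is that the described model omits an evident prognostic variable for a named hypothesis, and that a source for it is already in use.

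**Conclusion.** The point holds as a minor, optional improvement. As described, the adherence comparison has MOUD type as its only stated covariate and no term for adherence before randomisation. The cost is precision, not validity.

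At about 47 participants, the detectable difference is about 0.84 SD (even split) or 0.91 SD (29 v 15). Adjustment would lower 0.84 to between 0.80 and 0.60 SD across the assumed correlations. Even 0.60 SD is above the 0.54 SD for which the primary comparison is powered, so subset size is the larger limit and adjustment eases it only in part.

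This rests on four assumptions: that MOUD use in the past 12 months among the first 41 participants approximates the eventual subset; that the subset is fixed at baseline; that a linear model is adequate; and that the correlation lies between 0.3 and 0.7.

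**What to change.** 1. State that the MOUD subset consists of participants on MOUD at baseline.
2. Add to the adherence regression in MOUD analyses the adherence count for the 4 weeks before randomisation, defined as for the endpoint and taken from the pharmacy records already named as a source. Keep MOUD type in the model, and report the adjusted arm difference as the adherence result for this aim.
3. Where the records do not reach back, or MOUD began near entry, use the current-treatment information collected at baseline as a simpler covariate, or a missing-baseline indicator, so that no participant is dropped for want of a baseline count.
4. Settle this before outcomes are analysed.

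The cost is a short look-back in the records, one degree of freedom (one more if an indicator is used), and some incomplete baseline counts to handle. No visit, procedure or participant is added. If the correlation proves low, little is gained and little is lost.

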### Recruitment procedures

Participants are recruited from the Tuscaloosa VA Medical Center and the Birmingham VA Health Care System as they naturalistically present for treatment in vocational rehabilitation services, residential treatment program, outpatient mental health clinics, and addiction recovery programs, are referred to the study, respond to the IRB-approved advertisement/letter, or make personal inquiry into the study. During the 3-year enrollment period, we plan for at least 180 veterans to be directly offered consent, 140 to sign consent, 120 to be randomized, and 100 veterans to complete the study at the two sites. Participants are modestly compensated for each baseline and the bimonthly assessment visits.

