### Study limitations

The study protocol acknowledges several methodological challenges. Randomized controlled trials offer a robust design for evaluating intervention efficacy, but this approach is not without its limitations. Blinding among participants and study staff is not possible, given the nature of the IPS intervention. However, both IPS and non-IPS VR interventionists have received extensive training to ensure fidelity to intervention arms.

The study also faces potential limitations in terms retention of participants and generalizability. Veterans with OUD are a diverse group, and the study population may not fully represent the entire spectrum of this population. Data collection across multiple sites may introduce variability in intervention fidelity and outcome measurement, which could impact the overall findings.

Over the course of a multi-site trial, it can be challenging to maintain consistent follow-up because of attrition that may lead to missing data, potentially biasing the results. We minimize these potential limitations by keeping assessments to a minimum to reduce the burden on the participant. Finally, the study may be limited by resource constraints, including time and turn-over in personnel which could affect implementation of the intervention and data collection. Given that the sites are within 60 miles of each other and use shared technology, providing temporary coverage for study personnel turnover mitigates these vulnerabilities.

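### Both relapse outcomes accumulate with the number of TAPS visits attended, and neither is tied to observed time although about 17% are expected not to complete

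*Protocol article*

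**What the plan says.** The MOUD analyses section of the article defines two relapse outcomes for the third aim. The first: "Relapse will be treated in two ways, as a binary indicator if any relapse as determined by TAPS", with the threshold of at least four misuse occasions per month. The second is "the total number of self-reported days of misuse". The models are named: "The first dichotomous outcome will require logistic regression" and "The second approach will depend on the observed distribution and may be treated as either negative binomial or continuous". No observation window, time at risk, offset or early-exit rule is attached to either outcome.

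Two further analyses follow. One is a single sentence, "We will also explore the differences between groups in rates of relapse", which gives no denominator; the Data analyses section uses the word rates for percentages of categorical variables. The other is a set of exploratory longitudinal models of weekly adherence and relapse, with current and lagged employment as covariates.

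Follow-up visits are every two months to month 18, so there are nine after baseline (Randomization and follow-up schedule). Recruitment procedures plans for "120 to be randomized, and 100 veterans to complete the study at the two sites". Study limitations accepts that "it can be challenging to maintain consistent follow-up because of attrition that may lead to missing data, potentially biasing the results". An early-exit rule is written for employment only: weeks without data count as not worked (Primary outcome analysis).

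**The concern.** An ever-relapsed indicator and a running total of misuse days both depend on how long a person is watched. Someone seen nine times has nine chances to be recorded as relapsed and nine visits over which days add up; someone last seen at month 4 has two. The article chooses these cumulative forms and names their models, so the dependence on follow-up length comes from the stated outcomes and is not just a detail left unsaid.

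Lower relapse with IPS is one of the trial's stated hypotheses (Overview of design, aims, and hypotheses). If follow-up is incomplete, recorded relapse is too low in both arms. If it is also unequal, two arms with the same true risk will look different, and the arm that keeps more participants will look worse.

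**Working it through.** **What the documents supply.** Nine follow-up visits; 60 per arm; expected non-completion (120 − 100)/120 = 16.7%. They give no relapse risk, no loss by arm and no power figure for relapse, so there is no plan figure to reproduce. The expectation that more than 95% give analyzable data concerns employment, not TAPS.

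**Assumptions.** True relapse risk p per two-month interval is the same in both arms: p = 6%, range 3% to 10%. Loss over 18 months is L, at a constant hazard, so the chance of attending visit k is s^k with s = (1 − L)^(1/9). Outcomes are scored over attended visits.

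**1. True risk.** 1 − (1 − p)^9 = 1 − 0.94^9 = 42.7%.

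**2. Loss unrelated to relapse.** Recorded any-relapse is the sum over k = 1 to 9 of s^k (1 − p)^(k−1) p, which equals p·s·(1 − [s(1 − p)]^9) / (1 − s(1 − p)). Expected visits attended are the sum of s^k. With p = 6%:

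| Loss L | s | Recorded relapse | Mean visits |
|---|---|---|---|
| 8% | 0.9908 | 40.9% | 8.60 |
| 17% | 0.9795 | 38.9% | 8.13 |
| 26% | 0.9671 | 36.8% | 7.64 |

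- *Equal loss of 17% in both arms:* odds ratio 1.00, but 38.9% is recorded against 42.7% true.
- *Loss of 8% versus 26% (average 17%):* odds ratio (0.409/0.591)/(0.368/0.632) = 1.19.
- *Range:* p = 3% gives 22.9% versus 20.5%, odds ratio 1.15. p = 10% gives 58.9% versus 53.2%, odds ratio 1.26. Simulation of the same scenario gives 1.16 to 1.26, the same within rounding and simulation error.
- *Misuse days at equal daily rates:* ratio 8.60/7.64, about 1.12.

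**3. A different exit pattern.** Exits uniform over 18 months, loss 8% versus 25%, true 18-month risk 30% to 50%: odds ratio 1.13 to 1.16. The day ratio is (1 − 0.08/2)/(1 − 0.25/2) = 0.960/0.875 = 1.10.

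**4. Does a time-aware analysis help?** With loss unrelated to relapse, the relapse risk at each attended visit is p in both arms. A discrete-time model censored at last TAPS therefore returns an odds ratio of 1.00.

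**5. Exit triggered by relapse.** Assume 5% background loss, and that a first relapse causes exit before it is recorded with probability e. Recorded any-relapse is the sum of s^k (1 − p)^(k−1) p(1 − e), with s = 0.95^(1/9). For e = 10% versus 30% and p = 6%: 37.4% versus 29.1%, odds ratio 1.46 (1.36 to 1.62 for p from 3% to 10%). In the discrete-time model the odds at an attended visit are p(1 − e)/(1 − p), so the false odds ratio is 0.90/0.70 = 1.29 for every p. The model reduces this bias but does not remove it.

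**The case against.** The strongest reply is that this is a condensed article. An offset or a missing-data rule for a secondary aim usually sits in an analysis plan, and nothing here forbids one. That holds for the handling of missing data. It does not cover the choice of two cumulative person-level outcomes with their models, which the article makes itself.

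A reader might infer that the plan scores early leavers as relapse-free. The text does not say so. That is what happens if any and total are taken over attended visits; excluding leavers would instead raise a selection problem.

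A reader might also infer that IPS will retain more participants, because its job support continues while one control service's support typically ends once a job starts. Those passages describe vocational services. Research visits are on the same two-monthly schedule in both arms and are compensated, and participants who stop the intervention are encouraged to stay for assessments. Unequal loss is therefore an assumption with no source in the document. If IPS did retain more, the bias would run against the trial's hypothesis.

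The size is also limited. With 60 per arm, an odds ratio of 1.19 is about 0.47 standard errors, and a two-sided 5% test would reject about 7.6% of the time.

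The exploratory longitudinal models do use repeated observations. However, they condition on employment after randomization, so they do not estimate the overall effect of arm on relapse. Pharmacy records are named as a source alongside TAPS-2 and might continue after exit, but the two outcomes rest on TAPS and self-report.

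**Conclusion.** The point holds in a conditional form. The stated relapse outcomes accumulate with visits attended, and observed time enters neither. If they are scored over attended visits:

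- **Level:** relapse is understated in both arms, by about four percentage points (38.9% against 42.7%) at 17% unrelated loss and 6% risk per interval.
- **Comparison:** there is no bias between arms if loss is equal. At an assumed 8% versus 26% unrelated loss, the false odds ratio is about 1.15 to 1.26 and the day ratio about 1.12. The direction depends on which arm loses more.

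The larger figure of 1.46 needs relapse to trigger unrecorded exit at different rates by arm. The documents neither state nor exclude this, so it illustrates a risk and is not an expected bias. A better method is available on data already being collected, so the change is worth making.

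**What to change.** In MOUD analyses:

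1. Make the Aim 3 relapse comparison visit-based. Either code relapse yes/no at each attended TAPS visit and fit a repeated-measures logistic model, or fit a discrete time-to-first-relapse model censored at the last TAPS. Include arm, visit and site, and no employment covariates.
2. Analyse misuse days by negative binomial regression with the log of the days covered by completed TAPS as offset, and state how those days are counted.
3. Add a sensitivity analysis that counts exit as relapse, since steps 1 and 2 correct only loss unrelated to relapse.
4. Ever-relapse may still be reported alongside, with the number of visits attended by arm.

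The cost is revised wording and modest programming, with no new data collection. The article reports enrolment and follow-up as ongoing and presents no outcomes, so the change can still be written down in advance. The downside is small: the main result becomes a per-visit odds or hazard, which is less direct to read than a simple percentage.
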